### Data management {19}

Data management of the study will be carried out by the SZB (section Institute of Medical Biometry, Informatics and Epidemiology (IMBIE)). The study data is recorded and stored in a suitable, validated Clinical Data Management System (CDMS). Details on data management (procedures, responsibilities, data corrections, if any, which may be made by Data Management staff themselves, etc.) will be described in a *data management plan* prior to the trial. During the trial, the performance of data management and any deviations from the data management plan will be documented in a data management report. Queries and edit checks will be specified in a *data validation plan*. Before any data entry is performed, the trial database will be validated and the technical specifications of the database will be documented in a specific item list.

### Confidentiality {27}

The collection, transmission, archiving, and evaluation of personal data in this clinical trial are performed according to local applicable laws (Data Protection Act, General Data Protection Regulation). Prior to trial participation, each subject must be informed by the investigator about the purpose and extent of the collection and use of personal data, particularly medical data, and must give written informed consent.

The subjects must be informed that any subject-related data in this trial are handled confidentially and will be captured in pseudonymized form (subject ID number for the trial). It will only be transmitted to the coordinating investigator/sponsor/sponsor-delegated person/data monitoring safety board for scientific and adverse event evaluation and the responsible regulatory authority(ies) (local authority(ies)/BfArM or PEI), the Ethics Committees (ECs) of the trial sites and the European Data Base (EudraCT database) for verifying the proper conduct of the trial and for assessment of trial results and AEs.

During monitoring, audits, or inspections, representatives of the sponsor (monitor, auditor) or of the local regulatory authority(ies) must have direct access to personal data. In this case, the investigator is released from confidentiality. Consent to the collection and processing of personal data within the scope of this clinical trial can be withdrawn at any time. A patient is informed that she/he can terminate his/her participation in the clinical trial at any time—without giving reasons and without any following disadvantages. In the event of revocation of the declaration of consent, the data stored up to this point in time will continue to be used. This is necessary to determine the effects of the medicinal product under investigation and to ensure that the interests of the person concerned which are worthy of protection are not impaired, or to comply with the obligation to submit complete approval documents.

Individual participant data (including data dictionaries) that underlie results concerning primary or secondary endpoints reported in a published scientific article will be shared on demand after deidentification under the following conditions.

The data will be shared beginning 6 months and ending 3 years following article publication. Data are made available to researchers after a methodologically sound scientific proposal has been submitted to the coordinating investigator; a steering committee consisting of the coordinating investigator, the representative of the coordinating investigator, and a SZB member has approved the proposal; and a data access agreement has been signed. The study protocol and the informed consent forms will be made available on demand or through the website of the Division of Clinical Neurooncology, University of Bonn. After 36 months, the data will be available in our university’s data warehouse but without investigator support other than deposited metadata.

### Plans for collection, laboratory evaluation, and storage of biological specimens for genetic or molecular analysis in this trial/future use {33}

In phase I, patients receiving MFA and relapse tumor resection 7–10 days after initiation of study therapy will provide tumor material for determination of MFA/MFA metabolite tumor levels and analysis of cellular and molecular effects of MFA therapy according to internal standard operation procedures (SOPs) for tumor tissue acquisition and processing. MFA and metabolite measurements are performed under good clinical practice (GCP) conditions.

Patients receiving MFA and relapse tumor resection 7–10 days after initiation of study therapy will provide serum for determination of MFA/MFA metabolite serum levels on day 1 (2 h after first MFA intake) and on the day of tumor resection (prior to last MFA intake in the morning and 2 h, 4 h, 6 h, and 8 h later). Also, blood samples are drawn at baseline and at each timepoint with an MRI control to search for factors associated with tumor response, progression, and pseudoprogression.

## Statistical methods

### Statistical methods for primary and secondary outcomes {20a}

In phase I, the primary endpoint toxicity will be defined as incidence of DLTs and subsequent determination of the optimal dose for phase II and does not require extensive statistical analysis. To have robust results and the required number of patients with all necessary data for determining the phase II dose, early dropout patients/patients with insufficient data for 8-week DLT will be replaced. For secondary endpoints, additional analyses will include a post hoc analysis of the primary endpoint PFS as reviewed centrally by a neuroradiologist (Department of Neuroradiology, University Hospital Bonn).

In phase II, the primary outcome PFS is analyzed using a two-sided log rank test and a Cox regression analysis to estimate the hazard ratios in the intention-to-treat (ITT) population. PFS is measured from the day of randomization until the diagnosis of progressive disease determined by MRI (RANO criteria) in the local center.

OS is analyzed using a two-sided log rank test and a Cox regression analysis to estimate the hazard ratios in the ITT population. OS is measured from the day of randomization until death. Descriptive Cox regression analyses for common prognostic factors (age, KPS) and subgroup analyses for categorized common prognostic factors are also included. Phase II also includes descriptive statistics of all AEs (with reference to the number of patients and number of MFA/TMZ courses applied) during therapy. Dose reductions of TMZ, delay of TMZ therapy in subsequent courses, and premature withdrawals and development of KPS throughout the trial will also be described, as well as MFA/MFA metabolite tumor tissue and serum levels in patients resected after the start of MFA therapy are described.

QoL will be recorded using the standardized and validated EORTC QLQ-C30 and BN20 questionnaires [18]. The scores for the different dimensions will be compared between repeated assessments throughout the trial and between the two arms of the trial. As proposed in previous trials [19–21], domains of particular interest for brain tumor patients are preselected for particular consideration (global health status, physical functioning, social functioning, cognitive functioning, communication deficit, and motor dysfunction).

Additional details of the statistical analysis will be specified in the statistical analysis plan of the trial.

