### Trial design {8}

The study consists of a single-arm phase I part and a randomized, parallel-group, and unblinded phase II part.

In phase I, patients with the first relapse of MGMT-methylated glioblastoma are screened for the trial. After inclusion, patients are pretreated with MFA in addition to standard TMZ and tumor resection will be performed 7–10 days after initiation of therapy. MFA tissue level measurements and translational analyses are performed on the tumor material obtained from resection. Each patient is particularly screened for dose-limiting toxicities (DLTs) during the first 8 weeks of his/her MFA treatment. Patients are recruited in two cohorts of three to six patients. Dose adaptation in between cohorts depends on the occurrence of DLTs as described below.

All patients of phase I are followed for toxicity and efficacy until the end of phase II.

In phase II, patients with the first relapse of MGMT-methylated glioblastoma are screened for the trial. After inclusion, patients are randomized (1:1) into two parallel groups, the experimental or the standard treatment arm. The experimental treatment is defined as treatment with MFA (dose determined in phase I) in addition to standard TMZ. The standard treatment arm is defined as monotherapy with TMZ (150–200 mg/m^2^ body surface). If tumor resection for the relapsed tumor is clinically indicated, the local treating neurosurgeon can decide whether the resection can be safely postponed until day 7–10 after initiation of therapy (optional, not a prerequisite for study participation in phase II) and tumor material for determination of MFA levels can be obtained.

MFA is taken at the dose determined in phase I. Daily MFA treatment is continued for 8 4-week courses (i.e., 224 days), until tumor progression, until the occurrence of a DLT attributable to MFA, or until definitive discontinuation of standard TMZ, whatever comes first. In case MFA therapy is terminated, standard TMZ therapy can be continued at the discretion of the treating physician.

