### Sample size {14}

Phase I uses an adaptive design based on DLTs (see Fig. 1). Starting with 3(-6) patients per dose level is standard for dose finding in phase I. Starting with a middle-level MFA dose of 2 × 100 mg/day (according to the US registration of MFA) ensures that only two dose levels have to be explored (*n* = 6–12 patients). Patients not evaluable for DLT or MFA tumor levels will be replaced (conservative estimate, 1/6 patients; thus maximal patient number in phase I, 12 + 2 = 14).

The randomized phase II part accrues 30 patients per arm. For the evaluation of PFS, the experimental arm also includes the 3–6 patients of phase I which have been treated with the same dose of MFA as in phase II for an additional analysis. Since phase II is searching for indications of efficacy but is not a confirmatory trial, dropouts will not be replaced. In glioblastoma trials, the dropout rate is relatively low (e.g., 9% in CeTeG/NOA-09 trial). Therefore, and since data from dropout patients are included as censored observation, the results may be expected to be robust regarding patients with short follow-up/early dropouts.

With 30 subjects per arm and a two-sided alpha level of 10%, we could detect a hazard ratio of approximately 0.44 if we assume a PFS-6 of 40% for the reference treatment and use a power of 80%.

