## Assignment of interventions: allocation

### Sequence generation {16a}

The allocation to the treatment group in the phase II part will be performed electronically via the validated randomization tool of the electronic case report form (CRF) systemMARVIN (XClinical). The randomization will be performed using permuted blocks with a variable block size.

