### Implementation {16c}

The allocation sequence is generated randomly by the computer-based MARVIN randomization tool implemented by the statistician of the Clinical Study Core Unit Bonn (SZB). After input of all data necessary for randomization (inclusion/exclusion criteria, demographic data), the electronic system displays the randomization result.

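### The phase II primary PFS comparison names no baseline covariate or stratum; prespecified adjustment for age and KPS would be a cheap gain in robustness, with a power gain that is conditional

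*Protocol article*

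**What the plan says.** Section {20a} of the protocol article fixes the primary phase II analysis: "the primary outcome PFS is analyzed using a two-sided log rank test and a Cox regression analysis to estimate the hazard ratios". The population is intention-to-treat, and neither a covariate nor a stratum is named.

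In the paragraph on overall survival, the same section adds: "Descriptive Cox regression analyses for common prognostic factors (age, KPS) and subgroup analyses for categorized common prognostic factors are also included". It ends: "Additional details of the statistical analysis will be specified in the statistical analysis plan of the trial". Resection appears in no efficacy analysis.

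On allocation, section {16a} says: "The randomization will be performed using permuted blocks with a variable block size". No stratification factor is named. Section {16c} says: "After input of all data necessary for randomization (inclusion/exclusion criteria, demographic data), the electronic system displays the randomization result". Section {14} gives the size: "The randomized phase II part accrues 30 patients per arm".

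Section {10} admits adults with KPS from 60% upward. Phase II can include patients re-resected before randomization (Table 1, footnote 3), patients resected on day 7-10 of therapy (sections {8} and {13}) and patients not resected. Section {17a} makes the trial open label.

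**The concern.** The article itself calls age and KPS common prognostic factors, yet gives them no part in the primary comparison. Permuted blocks balance the arm sizes. They do not balance prognosis.

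Two things are at stake in a trial of 60 patients. First, a chance imbalance in a prognostic factor shifts the unadjusted hazard ratio, and a reader cannot separate that shift from a drug effect. Second, leaving strong prognostic factors out of a survival model pulls the estimated hazard ratio toward 1 and costs power.

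Resection also bears on how progression is measured. Patients re-resected before randomization need a postoperative baseline MRI, so their reference scan for RANO differs in kind from that of the others.

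**Working it through.** **Inputs from the article.** 30 per arm, two-sided alpha 10%, power 80%, control PFS-6 40%, detectable hazard ratio about 0.44 (section {14}); follow-up of at least 6 months after the last randomization (section {13}). The length of phase II accrual is not stated, because the recruitment dates cover both phases. No covariate strengths are given.

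**Assumptions.** Exponential PFS; accrual of 12 months (18 months as a check); age standardised normal; low KPS and resection status each at 50% prevalence; strengths as listed below.

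**1. The plan's own figure.** Events needed at HR 0.44, with z-values 1.645 and 0.842 (sum squared 6.18):
- Schoenfeld: 4 × 6.18 / (ln 0.44)² = 24.7 / 0.674, giving 37 events.
- Freedman: (1.44 / 0.56)² × 6.18 = 6.61 × 6.18, giving 41 events.

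The control hazard is -ln(0.40) / 6 = 0.153 per month. With 12 months' accrual plus 6 months' follow-up, the expected event probability is 0.817 in the control arm and 0.541 in the experimental arm, so 30 × (0.817 + 0.541) = 40.7 events. The detectable hazard ratio is then 0.439 (Freedman) or 0.461 (Schoenfeld). The stated 0.44 reproduces under this assumed accrual.

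**2. Chance imbalance.** For a factor with prevalence p, the difference in counts between arms has variance 2 × 30 × p(1-p). With a continuity correction:
- p = 0.4: SD = √14.4 = 3.79; 5.5 / 3.79 = 1.45; P(difference of 6 or more) ≈ 0.147.
- p = 0.5: SD = √15 = 3.87; 5.5 / 3.87 = 1.42; P ≈ 0.156.

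These count both directions. Either direction alone is about 7-8%.

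**3. What such an imbalance does when the drug has no effect.** Median hazard ratio in simulated trials with a difference of 6 or more in the resection factor, by direction (10,000 trials per setting before selection):

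| Factor HR | Unadjusted | Adjusted |
|---|---|---|
| 1.5 (moderate) | 0.92 / 1.10 | 1.01 / 1.00 |
| 2 (strong) | 0.87 / 1.14 | 0.99 / 1.01 |

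**4. Power at a conditional HR of 0.44** (10,000 trials per setting, about 40 events). Strengths are HR per SD of age / for KPS / for resection.

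| Strength | Log-rank | Log-rank stratified by resection | Cox adjusted for all three (Wald) | Adjusted minus log-rank |
|---|---|---|---|---|
| None | 82.8% | 81.3% | 81.7% | -1.1 |
| Weak (1.15/1.25/1.25) | 81.9% | 81.0% | 81.6% | -0.3 |
| Moderate (1.3/1.5/1.5) | 78.2% | 77.8% | 81.5% | +3.3 |
| Strong (1.5/2/2) | 70.9% | 72.2% | 80.6% | +9.7 |

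With 18 months' accrual (4,000 trials per setting) the differences are -1.7 (none), +3.9 (moderate) and +10.9 (strong), so the pattern does not hang on the accrual assumption.

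**5. Size under no drug effect, nominal 10%.** Log-rank 9.8-10.9%; stratified log-rank 10.0-10.7%; adjusted Cox with a Wald test 11.4-12.0%.

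**The case against.** The strongest reply has four parts.

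- **The plan is valid and exploratory.** Section {14} says that phase II is not confirmatory. The log-rank test holds its level with chance imbalance already included in the calculation. This stands. A reader might infer that the primary test is wrong or biased, and the documents do not support that.
- **Covariates belong in the SAP.** The article defers further detail, and the full protocol could name strata. This stands in part. What is deferred is additional detail, while the test and the descriptive role of age and KPS are already stated. That the comparison is unadjusted and unstratified still rests on a condensed article naming no factor.
- **The power argument is soft.** A reader might infer that adjustment would recover power as a matter of course. It does so only if the factors are at least moderately prognostic, and the article gives no strengths. Part of the gain comes from the liberal Wald test. The simulation also sets 0.44 as the hazard ratio conditional on covariates, whereas section {14} gives it for a plain two-arm comparison. Stratifying by resection alone gains almost nothing. All of this stands.
- **Resection is not simply a baseline factor.** A reader might infer that resection is collected and can be adjusted for like age. Surgery on day 7-10 is decided after randomization in an open-label trial and may depend on arm, so adjusting for it could introduce bias. That status before randomization is recorded is only inferred from a footnote, since the body of Table 1 is not shown. This stands and limits the fix.

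It would also be too much to call a large imbalance likely: about 15% is a material risk, not an expectation.

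**Conclusion.** The point holds as a recommended improvement, not as an error. As stated, the primary PFS comparison makes no use of prognostic information that the article itself recognises, in a trial small enough for this to matter.

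The firmer benefit is robustness. In roughly one trial in seven, a factor with 40-50% prevalence will differ by 6 or more patients of 30, and the unadjusted hazard ratio then shifts by about 8-14% under an assumed factor hazard ratio of 1.5 to 2. Adjustment removes nearly all of that shift.

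The power benefit is conditional: from a loss of about 1 point to a gain of about 10, depending on strengths that the article does not give. These figures come from a model with all three factors. A model with age and KPS alone would gain less if resection is prognostic, and would not protect against imbalance in resection.

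**What to change.** 1. Prespecify, before outcome data by arm are seen, that the PFS treatment effect comes from a Cox model with arm, baseline age (continuous) and baseline KPS.
2. Test the arm term with a score or likelihood-ratio test in place of the Wald test. The calculations above measured size for the Wald test only, so confirm the chosen test's size by simulation at this sample size.
3. Keep the unadjusted log-rank test and Cox hazard ratio as named sensitivity analyses.
4. If resection status (already re-resected, resection intended, none intended) is recorded before randomization, add it as a covariate and, if feasible, as a randomization stratum.
5. State that resection performed on day 7-10 will not be used as an adjustment covariate.

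The cost is a paragraph of analysis text, plus one field in the randomization tool if resection is used. Age is demographic and KPS is an eligibility item, so both should be at hand at randomization. The downsides are small: the adjusted hazard ratio is conditional on the covariates and must be reported as such, and up to about a point of power is lost if the factors turn out not to be prognostic.

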### Outcomes {12}

In phase I, the primary outcome to be evaluated will be the incidence of DLTs during the first 8 weeks of MFA treatment. DLT for each dose level is defined as any CTCAE5 grade 3/4 organ toxicity or grade 4 hematotoxicity > 2 weeks during the first 8 weeks of MFA treatment; events probably related to the tumor resection and/or perioperative treatment or to the underlying disease are not regarded as DLT. Secondary outcomes in phase I are progression-free survival (PFS) as measured from the inclusion into the trial until diagnosis of progressive disease determined by MRI (according to “response assessment for neurooncology” (RANO) criteria) in the local center, PFS according to post hoc central reference neuroradiological assessment, overall survival (OS) as measured from the day of inclusion into the trial, assessment of safety beyond 8-week MFA treatment, and Karnofsky Performance Score (KPS), Quality of life (QoL), and Mini-Mental State Examination (MMSE) throughout the trial.

In phase II, the primary outcome to be evaluated will be PFS (randomization until the diagnosis of progressive disease according to RANO criteria). Secondary outcomes will be OS (randomization until death), continuous monitoring of AE/severe adverse events (SAE)/suspected unexpected serious adverse reactions (SUSARs), and quality of life throughout the trial (measured by KPS, QoLs, and MMSE). Survival analyses also include patients from phase I who received MFA at the same dose as applied in phase II.

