### Methods in analysis to handle protocol non-adherence and any statistical methods to handle missing data {20c}

In phase I, patients who are not evaluable for DLT will be replaced. A patient is evaluable for DLT if the DMSB has determined that a DLT has occurred in this patient during the first 56 days after treatment start (independent of the duration of MFA intake) or if until DLT visit (day 56 ± 3 days after start of MFA treatment) the patient has taken at least 100 doses of MFA (i.e., 89.3% of the maximally positive cumulative dose in 56 days) as documented by the patient’s diary and the documented return of 1 empty container of MFA (containing 100 capsules) (for dose step 2 × 100 mg daily or 2 × 50 mg daily) or of 2 empty containers of MFA (for dose step 2 × 200 mg daily).

In phase II, subjects dropping out of the trial prior to randomization will be listed as screening failures including the reason for dropout. Subjects prematurely discontinuing the trial will be censored regarding the analysis of PFS or OS at the time of discontinuation. Subjects dropping out after randomization will be analyzed using all available data and will not be replaced. The technique for the analysis of missing values will be defined in the statistical analysis plan. A check of a possible treatment effect on the frequency of missing values will be performed.

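### The primary endpoint called PFS ends only at progressive disease and does not name death as an event, so as written it measures time to progression

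*Protocol article*

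**What the plan says.** The protocol article defines PFS three times.

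- Statistical methods {20a}, phase II: "PFS is measured from the day of randomization until the diagnosis of progressive disease determined by MRI (RANO criteria) in the local center".
- Outcomes {12}, phase II: "the primary outcome to be evaluated will be PFS (randomization until the diagnosis of progressive disease according to RANO criteria".
- Outcomes {12}, phase I, as a secondary outcome: "as measured from the inclusion into the trial until diagnosis of progressive disease determined by MRI".

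None of the three mentions death. For overall survival, {20a} does: "OS is measured from the day of randomization until death".

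On the analysis, {20a} states that "the primary outcome PFS is analyzed using a two-sided log rank test and a Cox regression analysis" in the ITT population. On patients who leave, section {20c} says "Subjects prematurely discontinuing the trial will be censored regarding the analysis of PFS or OS at the time of discontinuation". Its next sentence says that those who drop out after randomization are analyzed with all the data available and are not replaced. The sample size section {14} likewise relies on dropouts being censored ("since data from dropout patients are included as censored observation"). MRI is scheduled every 8 weeks, both during and after study therapy (Participant timeline {13}).

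**The concern.** Progression-free survival should end at progression or death, whichever comes first. Here the event is fixed in the text as progressive disease alone. In a log-rank or Cox analysis, a patient who dies before a documented progression then has no event, and the only place left for that patient is among the censored. That treats a death as if the patient could still have been observed to progress later.

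Two smaller problems sit next to this. First, {20a} requires progression to be determined by MRI, while the phase II definition in {12} asks only for RANO criteria. Whether a deterioration not shown on MRI can count therefore depends on which section is followed. Second, PFS is censored at the date of leaving the trial and not at the last tumor assessment, so time without imaging counts as progression-free.

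At stake is what the primary result means. Survival curves would look better in both arms than true PFS. If deaths without documented progression were unequally distributed, the hazard ratio would be distorted as well.

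**Working it through.** **1. The plan's own figure.** Section {14} states: "With 30 subjects per arm and a two-sided alpha level of 10%, we could detect a hazard ratio of approximately 0.44", with control PFS-6 of 40% and power of 80%. By Schoenfeld's formula the events needed are 4 × (1.645 + 0.842)² / (ln 0.44)² = 4 × 6.18 / 0.674 = 36.7, so 37. With exponential PFS the control hazard is −ln(0.4)/6 = 0.1527 per month (median 0.693/0.1527 = 4.54 months). The phase II accrual time is not stated. If it is 12 months, followed by the stated minimum of 6 months, 40.7 events are expected at HR 0.44. The figure of 0.44 reproduces with accrual of roughly 6 to 12 months, depending on the formula. It is not in error.

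**2. Effect on the curve.** Let q be the share of first PFS events that are deaths without documented progression. The protocol gives no value, so 5, 10 and 20% are assumed. With constant hazards and these deaths not counted, apparent PFS-6 is 0.4^(1−q) and the apparent median is 4.54/(1−q).

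| q | apparent PFS-6 | apparent median (months) |
|---|---|---|
| 0 | 40% | 4.5 |
| 5% | 42% | 4.8 |
| 10% | 44% | 5.0 |
| 20% | 48% | 5.7 |

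**3. Effect on power.** Counted events are (1−q) times the true number, and power is Φ(|ln 0.44| × √(d/4) − 1.645). If exactly 37 true events were available:

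| q | counted events d | power at HR 0.44 |
|---|---|---|
| 0 | 37 | 80.3% |
| 5% | 35.1 | 78.5% |
| 10% | 33.3 | 76.5% |
| 20% | 29.6 | 72.2% |

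Longer accrual gives a margin. At q = 20%, 12 months of accrual gives 40.7 × 0.8 = 32.6 events (power 76%), and 18 months gives 44.3 × 0.8 = 35.4 (79%).

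**4. Effect on the hazard ratio.** The apparent ratio is the true PFS ratio times (1 − q on MFA)/(1 − q on control).

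- Equal shares: the factor is 1, so there is no bias.
- 10% on control, 20% on MFA, true HR 1: 0.8/0.9 = 0.89, in favor of MFA.
- The reverse: 0.9/0.8 = 1.13, against MFA.

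The same can be put from the other side. Suppose the progression HR is 0.44 and deaths are 10% of control first events. With a death HR of 1, the true PFS HR is 0.9 × 0.44 + 0.1 × 1 = 0.50. With a death HR of 2, it is 0.9 × 0.44 + 0.1 × 2 = 0.60. The endpoint as written would show about 0.44 in both cases.

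**5. The censoring rule.** With 8-weekly MRI, a patient who leaves just before the next scan is credited with up to about 8 weeks that nobody imaged. If the 9% dropout cited in {14} from an earlier trial applied here, this would concern 0.09 × 60 = 5.4, so about 5 patients.

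**The case against.** The article is condensed, it uses the established name of the endpoint, and it leaves further statistical detail to an SAP that is not shown. The authors may well intend to count deaths. That defense would work if the event had been left open. It has been stated, three times, and an SAP that added death would change the protocol's definition of its primary endpoint.

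Several stronger readings are tempting, and the document does not support them.

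- *Deaths are planned to be censored.* No section says so. The rule in {20c} concerns patients who discontinue the trial and does not mention death. Non-counting follows from the event definition together with the method of analysis.
- *Clinical progression is excluded throughout.* The MRI limit stands in {20a} and in the phase I definition, but not in the phase II definition in {12}. The stopping criteria in {11b} pair RANO with MRI signs, which points one way without settling it. This is an inconsistency between sections.
- *Outcome data collected after departure are thrown away.* Section {18b} keeps patients who stop treatment in follow-up. For those who refuse, it asks for outcomes to be documented around an early termination visit, if possible. It does not promise later data on them. The censoring rule therefore touches few patients, and for OS the departure date may be close to the last date known alive.
- *The false-positive rate doubles.* Simulation under a true null with shares of 10% and 20% does give about 10% false claims for MFA against 5% with deaths counted. This only carries forward the assumed doubling in the MFA arm. The protocol acknowledges a gastrointestinal bleeding risk under MFA, but gives no figure that would support that imbalance.

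It is also fair that the share may be low. Entry requires life expectancy above 6 months and KPS of at least 60%, and the background section puts median PFS at about 3 months against OS of 10–12 months. Phase II is declared non-confirmatory, and OS is tested separately, so an excess of deaths would be visible there. These points limit the likely size. They do not make the primary endpoint PFS.

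**Conclusion.** The point stands as a defect in the definition of the primary endpoint. Following the text exactly yields time to progression under the name of PFS, because death is an event only for OS. The MRI and RANO wordings disagree, and the two sentences on dropouts in {20c} need to be reconciled.

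The size cannot be fixed from the document. For assumed shares of 5 to 20% and constant hazards, PFS-6 is overstated by 2 to 8 percentage points in an arm whose true value is 40%. The loss of power is modest and depends on an accrual time that is not stated. The hazard ratio is biased only if the share differs between arms, and the bias can go either way. The sample size figure of 0.44 is not disputed.

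**What to change.** - In {12} and {20a}, use one identical definition: time from randomization (phase I: from inclusion) to the first of progression by RANO criteria or death from any cause.
- Reconcile the MRI-only and RANO wordings, so that it is clear whether a deterioration not shown on MRI can count.
- In {20c}, reconcile the censoring sentence with the one after it. Censor patients without a PFS event at their last evaluable tumor assessment, and censor OS at the last date known alive.

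The cost is wording only. Dates of death and MRI are already collected, and neither the sample size nor the visit schedule changes. Because this concerns the primary endpoint, it should be settled before the phase II data are analyzed.
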